### Adverse events and safety monitoring

2.12

All adverse events (AEs) will be recorded in the case report form (CRF) and managed within 24 hours. A study physician will evaluate each AE and document AE type, onset/duration, management, outcome, CTCAE grade (1–5), and causality (definitely/probably/possibly/unlikely/unrelated).

AEs will be graded according to the Common Terminology Criteria for Adverse Events (CTCAE): Grade 1 (mild), Grade 2 (moderate), Grade 3 (severe), Grade 4 (life-threatening), and Grade 5 (death). Serious adverse events (SAEs) (fatal, life-threatening, requiring/prolonging hospitalization, or causing persistent/significant disability) and emergencies will be reported to the ethics committee and relevant institutional personnel within 24 hours of awareness.

Participants may withdraw at any time; investigators may discontinue the intervention if continuation is deemed unsafe. Participants experiencing AEs will be followed until stabilization/resolution. The principal investigator will review AE reports regularly, and a safety review meeting will be convened if necessary. Potential acupuncture-related AEs include syncope, needle retention/breakage, local hematoma, and localized infection; participants with severe intervention-related AEs will be withdrawn immediately.

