### Sample size

2.9

This study is designed as an exploratory, mechanism-oriented neuroimaging trial. At present, there are limited prior data from sham-controlled acupuncture studies in post-stroke dysphagia that combine multimodal MRI outcomes with comparable clinical endpoints, which makes a formal power calculation based on a single anticipated effect size difficult. Therefore, the planned sample size was determined with reference to previous neuroimaging studies, practical feasibility, and the exploratory nature of the present protocol. Given the characteristics and high costs associated with neuroimaging studies, sample sizes are generally smaller compared with conventional clinical trials, and there is currently no standardized consensus regarding the minimum sample size required to achieve stable statistical power. A study in 2002 reported that a sample size of 12 subjects was sufficient to provide relatively stable statistical power in rs-fMRI research (39). In 2007, another study using auditory stimulation of rs-fMRI suggested that a sample size of 13–15 subjects was adequate for stable statistical inference (40). In 2011, investigators compared sample sizes of 5, 8, 14, 17, and 21 subjects under otherwise consistent conditions. They observed that smaller sample sizes (e.g., 5 or 8) produced fewer activation regions with greater variability, whereas larger sample sizes yielded more activation clusters and reduced intergroup differences (41). Ultimately, the literature recommends that, where ethically and practically feasible, neuroimaging trials should include at least 20 subjects per group (42).

Taking into account the constraints of study duration, patient hospitalization time, and available manpower, and with reference to previous clinical research, we determined that a randomized controlled trial with 20 participants per group (40 in total) would be appropriate. Considering an expected 15% dropout rate, the final planned sample size is 46 participants [40 × (1 + 15%) = 46].

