### Data collection

2.10

Data collection will be performed by therapists employing standardized CRFs. Two independent researchers will then enter the data into a secure database. All analyses will be conducted under the supervision of an independent data monitor to ensure accuracy, consistency, and data integrity. For participants who withdraw, their number and reasons (particularly those related to AEs) will be carefully documented.

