#### Clinical data analysis

2.11.2

All randomized participants will be included in the preliminary analysis according to the intention-to-treat (ITT) principle. Data will be analyzed with SPSS v25.0 (IBM, Armonk, NY, USA). A two-tailed *p*-value of ≤ 0.05 will be taken to indicate statistical significance, and continuous data will be reported as mean ± standard deviation (SD). For normally distributed continuous variables, an independent-samples *t*-test will be used, whereas for non-normally distributed data, the Mann–Whitney *U* test will be applied. Categorical and ordinal variables will be expressed as percentages (%) and analyzed using the chi-square test when expected cell counts are adequate (typically all expected counts ≥5), or Fisher's exact test when expected counts are small. Ordinal data will be analyzed using the rank-sum test.

The incidence of adverse events will be summarized in the safety analysis and compared between groups using the chi-square test or Fisher's exact test, as appropriate. Missing data for participants who withdraw or deviate from the protocol will be handled using listwise deletion or multiple imputation methods.

fMRI data will be analyzed by experienced imaging specialists. All statistical analyses will be performed by independent data analysts who are blinded to group allocation, thereby minimizing potential bias.

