**Figure 3 F3:**
[figure not shown]
SPIRIT schedule of enrolment, interventions, and assessments. EOT, End of Treatment; rs-fMRI/DTI at baseline (t0), and Week 6; SSA at t0/Weeks 2/4/6; VFSS/MoCA/SWAL-QOL at t0 and Week 6; AEs monitored throughout.

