### Trial status

2.15

The trial is now in its recruitment period, and the first subject was enrolled on 23 July 2024. Recruitment is planned to continue until 31 December 2025, and each participant will be followed for 6 weeks after enrolment. The current protocol version is 1.1 (dated 17 October 2025). At the time of manuscript submission, patient enrolment and follow-up are ongoing; the data remain blinded and no primary outcome analyses have been conducted.

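### Mandatory withdrawal after a severe intervention-related adverse event can cost the week-6 primary outcome, although only the needling needs to stop

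*Protocol article*

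**What the plan says.** Section 2.12 contains two differently worded actions in one paragraph. The first is discretionary and concerns treatment: "investigators may discontinue the intervention if continuation is deemed unsafe". The second is mandatory and concerns the participant: "participants with severe intervention-related AEs will be withdrawn immediately". It applies to both arms. The only follow-up secured there is of the adverse event itself, until it stabilizes or resolves.

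Other sections bear on what withdrawal means:

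- Section 2.10: "For participants who withdraw, their number and reasons (particularly those related to AEs) will be carefully documented". Nothing is said about outcome data for them.
- Section 2.11.2: "Missing data for participants who withdraw or deviate from the protocol will be handled using listwise deletion or multiple imputation methods".
- Section 2.11.2 also states: "All randomized participants will be included in the preliminary analysis according to the intention-to-treat (ITT) principle".
- Section 2.15, in a general description of trial status: "each participant will be followed for 6 weeks after enrolment".
- Figure 3 legend: "rs-fMRI/DTI at baseline (t0), and Week 6". Section 2.7.2 defines the primary outcomes as changes between these two time points.
- Section 2.9: "Considering an expected 15% dropout rate, the final planned sample size is 46 participants".

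**The concern.** A severe reaction to needling is a good reason to stop needling. It is not in itself a reason to stop measuring outcomes. Section 2.12 does not keep these apart for the patients in whom the distinction matters most, and nothing in the article secures their week-6 scan or clinical assessments.

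If the sentence is followed in its stricter sense, the protocol itself creates missing outcomes that depend on treatment tolerance. If such events were more frequent in one arm, that arm's result would move from the effect in everyone randomized toward the effect in those who tolerated treatment. That fits badly with an intention-to-treat analysis. An imbalance is plausible: the active arm has skin penetration and deliberate slight mucosal bleeding, while the sham needles do not breach the skin, so hematoma, infection and needle breakage would be expected mainly in the active arm. Syncope, also listed in section 2.12, needs no skin breach and could occur in either.

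**Working it through.** **Which reading the text supports**

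- Toward leaving the study: section 2.12 has its own phrase for stopping the intervention and does not use it in the mandatory rule. Section 2.10 keeps only counts and reasons for those who withdraw. Section 2.11.2 links withdrawal to missing data.
- Toward stopping treatment only: section 2.15 describes 6 weeks of follow-up for each participant. It is a general statement and sets no rule for withdrawn participants.

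The text leaves two readings. The stricter one is the more natural, and it is the one carried by an explicit instruction.

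**What is lost on the stricter reading**

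MRI is acquired at baseline and week 6 only. A patient withdrawn during treatment has no post-baseline scan. Listwise deletion drops the patient, and a mixed model or imputation has no observed primary outcome from that patient to use.

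**The plan's own figure**

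Section 2.9: 40 × (1 + 0.15) = 46, which reproduces. The allowance is 46 − 40 = 6 patients, nominally 3 per arm. Each withdrawal under this rule uses one of them.

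**How often the rule might apply**

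The article gives no rate of severe intervention-related events, so the rate r per patient is an assumption. P(at least one among n) = 1 − (1 − r)^n.

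| Assumed r | n = 46 (both arms) | n = 23 (one arm) |
|---|---|---|
| 1% | 37% | 21% |
| 2% | 61% | 37% |
| 5% | 91% | 69% |

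**How far an arm mean could move**

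Assume that k of a nominal 23 active patients are lost and none in sham, and that the lost patients would have differed from the rest by d SD. The shift is (k/23) × d.

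- k = 1, d = 0.5: 0.043 × 0.5 = 0.022 SD
- k = 3, d = 1.0: 0.130 × 1.0 = 0.130 SD

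The standard error of the difference between arms, in SD units:

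- 22 against 23: √(1/22 + 1/23) = 0.298
- 20 against 23: √(1/20 + 1/23) = 0.306

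The shift relative to the standard error is 0.022/0.298 = 0.07 to 0.130/0.306 = 0.43.

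If one such patient is also lost in sham, the net shift is ((k − 1)/23) × d: 0 for k = 1, and 2/23 × 1.0 = 0.087 SD for k = 3 and d = 1.0. With equal numbers and equal d, or with no such events, it is zero.

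**Expected rather than conditional size**

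Averaged over the chance that events occur at all, with losses in the active arm only, the shift is r × d. For r of 1% to 2% and d of 0.5 to 1.0 this is 0.005 to 0.02 SD. Against √(2/23) = 0.295 that is about 0.02 to 0.07 of a standard error.

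**The case against.** The strongest objection is that the sentence does not say what the participant is withdrawn from. It follows a list of needling-related events in a safety section, so withdrawal from needling is a possible meaning, and section 2.15 speaks of 6 weeks of follow-up without exception. A journal article may also leave post-discontinuation data collection to the full protocol. This stands as far as showing that the text is ambiguous. It does not remove the point, because the published sentence is a positive instruction that leans toward loss, not a silence.

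Second, the trigger is narrow (both severe and intervention-related), the introduction describes acupuncture as safe and well tolerated, and the trial is exploratory with a dropout allowance that would cover a few cases. This stands: the expected effect is small, and even the unfavourable scenario stays below half a standard error. Neither an imbalance between arms nor the direction of any shift can be shown.

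Third, intention-to-treat and multiple imputation are compatible, and imputation could draw on the baseline scan, covariates and any SSA scores collected before the event. That is correct, but it replaces an observable week-6 scan with a model-based one, and listwise deletion remains the stated alternative.

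Fourth, some of these patients will decline to return or be unfit for MRI or VFSS, so only part of the loss is recoverable. That also stands.

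**Conclusion.** The concern holds, with low practical weight. On its more natural reading, section 2.12 turns a severe intervention-related event into a missing primary outcome, and the article contains no provision that prevents this. Given that 1 to 3 of 23 active patients are lost with none in sham and d is 0.5 to 1.0 SD, the active-arm mean shifts by 0.02 to 0.13 SD (0.07 to 0.43 of a standard error). The shift is smaller or zero if losses are balanced or no such events occur. All of these inputs are assumptions. The case for change rests on the loss being at least partly avoidable at very low cost, not on a demonstrated bias.

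**What to change.** In section 2.12, replace the withdrawal clause with a rule of this kind: a participant with a severe intervention-related adverse event stops the study intervention immediately but stays in the trial unless consent for follow-up is withdrawn. Where medically feasible, the participant completes the remaining SSA visits and the week-6 rs-fMRI/DTI, VFSS, MoCA and SWAL-QOL, timed from randomization, and is analysed in the assigned arm.

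In section 2.10, record the date and reason for stopping the intervention separately from study withdrawal.

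The cost is one change of wording and one case report form field, since the assessments are already scheduled. The decision to stop needling, and so patient safety, is unaffected. The burden is that some patients who have stopped needling must be asked to return at week 6, and a few will decline or be unfit.

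Section 2.15 planned recruitment to end on 31 December 2025, so the change may come too late for some or all participants. In that case the report should state which reading was applied, and count intervention stops separately from study withdrawals by arm.

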### SPIRIT compliance

2.13

This protocol adheres to SPIRIT 2013; the completed SPIRIT checklist and the SPIRIT figure are provided in the Supplementary material. Figure 3 summarizes the enrolment, intervention and evaluation calendar (SPIRIT).

**Figure 3 F3:**
[figure not shown]
SPIRIT schedule of enrolment, interventions, and assessments. EOT, End of Treatment; rs-fMRI/DTI at baseline (t0), and Week 6; SSA at t0/Weeks 2/4/6; VFSS/MoCA/SWAL-QOL at t0 and Week 6; AEs monitored throughout.

### Data monitoring committee (DMC)

2.14

DMC consists of experienced biostatisticians from Guangzhou University of Traditional Chinese Medicine. They do not participate in daily research or data processing of the study. The committee is responsible for periodically reviewing trial conduct, recruitment, data completeness and quality, protocol adherence (including adherence to allocation concealment procedures), adverse events, the safeguarding of participant privacy, and overall participant safety. Based on these reviews, the DMC may provide independent recommendations to the principal investigator and the Medical Ethics Committee on whether the trial should continue as planned, be modified, or be terminated early. The DMC operates independently of the investigators and has no competing interests related to this study.

### Trial status

2.15

The trial is now in its recruitment period, and the first subject was enrolled on 23 July 2024. Recruitment is planned to continue until 31 December 2025, and each participant will be followed for 6 weeks after enrolment. The current protocol version is 1.1 (dated 17 October 2025). At the time of manuscript submission, patient enrolment and follow-up are ongoing; the data remain blinded and no primary outcome analyses have been conducted.

## Discussion

3

Currently, acupuncture has demonstrated significant efficacy in the treatment of PSD and is recommended in clinical guidelines (16); however, its central mechanisms remain unclear. Previous fMRI-related studies have primarily focused on the activation effects of acupuncture on PSD brain regions, whilst in-depth exploration of the mechanisms underlying functional network reorganization remains relatively limited (51). This study employs multimodal rs-fMRI and DTI to investigate the mechanisms of brain functional network reorganization in patients with PSD treated with Tiao Shen Li Yan acupuncture. To our knowledge, this is the first study to elucidate changes in acupuncture-induced brain functional connectivity patterns and structural alterations in inter-network white-matter pathways, thereby exploring the underlying structure-function coupling mechanisms, while also using healthy individuals as imaging baseline controls to define PSD-specific network alterations. Through objective neuroimaging evidence and clinical data, this study aims to provide crucial support for advancing acupuncture research and clinical practice.

The Tiao Shen Li Yan acupuncture is grounded in traditional Chinese medical (TCM) pathophysiology, centered on the notion that dysregulation of the “Yuan-Shen” (vital spirit) disrupts the guidance of qi and thereby impairs pharyngeal function. Anchored in the TCM holistic view that the brain is the residence of the Yuan-Shen and governs the whole body, the therapy operates on two levels. At the systemic level, modulation of the Yuan-Shen is intended to restore normal central control of swallowing. At the local level, “facilitating the pharyngeal orifices” aims to improve swallowing function; in addition, needling of throat-related acupoints provides afferent feedback that may promote reorganization within the central swallowing circuitry. This synergy between systemic and local interventions is designed to comprehensively recalibrate swallowing function and thereby enhance therapeutic efficacy. Experimental evidence suggests that electroacupuncture at Lianquan (CV23) can activate excitatory neurons in the primary motor cortex and modulate swallowing-related musculature via the M1-parabrachial nucleus-nucleus tractus solitarius pathway, improving swallowing function (52). Furthermore, acupuncture at Fengchi (GB20) has been reported to ameliorate dysphagia by modulating cerebral blood flow and neural function (53). The acupoints Baihui (GV20), Shenting (GV24), and Yintang (EX-HN3)—key nodes for regulating “shen” in stroke rehabilitation—have been associated with anti-inflammatory effects, network-level neuromodulation, and improved cerebral circulation (54). Patients with PSD often present with varying degrees of cognitive impairment (31), which in traditional Chinese medicine may be interpreted as a disturbance of “Shen.” Accordingly, the MoCA will be used as a clinical outcome measure to evaluate changes in cognitive function. In combination, these acupoints provide a multi-target therapeutic strategy for PSD, collectively achieving the intended effect of “regulating shen and facilitating the throat.” Although our preliminary clinical work has demonstrated the clinical efficacy of the Tiao Shen Li Yan acupuncture approach in PSD, its central mechanisms remain to be elucidated (8).

Post-stroke dysphagia (PSD) occurs when cerebral infarction disrupts the distributed neural system that supports swallowing, leading to abnormalities in both network connectivity and white-matter integrity. Importantly, converging neuroimaging evidence suggests that PSD is best conceptualized as a network-level disorder rather than a focal lesion effect, involving coordinated dysfunction across cortical and subcortical hubs. At the cortical level, swallowing-related control engages the sensorimotor cortex (M1/S1/S2), SMA, and frontal regions (including IFG), and interacts closely with subcortical structures such as the thalamus, insula, and basal ganglia, as well as bottleneck white-matter regions (e.g., corona radiata/internal capsule) (55). Recent work has further described modular organization within the swallowing connectome (e.g., insula, cerebellum, sensorimotor–cingulate, IFG–S2–corpus callosum–basal ganglia–thalamus, and premotor–posterior parietal modules), which can be arranged into higher-order circuits supporting swallowing control and compensation (55). Notably, prior rs-fMRI studies in PSD have reported both regional activity alterations and connectivity abnormalities across these hubs, including the sensorimotor cortex, insula, cerebellum, cingulate, thalamus, and basal ganglia (56). Across studies, the most frequently implicated loci include the insula, basal ganglia, frontal cortex, M1, SMA, corona radiata, and S1(57). However, brain network–level evidence remains limited, and existing studies have only partially examined how these regions reorganize as integrated circuits during recovery. For example, rs-fMRI and fNIRS studies suggest abnormalities in DMN and reduced connectivity between the frontal–temporal–sensory–motor circuit and the sensory–motor–insular–thalamic circuit; moreover, altered insula–cerebellum–occipital functional connectivity has been associated with dysphagia severity (51, 58).

Therefore, in the present study we explicitly separate primary and secondary analyses. The primary (confirmatory) analyses anchor structure-function coupling tests to a prespecified ROI set that captures core swallowing-related hubs with consistent PSD abnormalities (insula, basal ganglia, frontal cortex, M1, SMA, corona radiata, and S1). The secondary (supportive) analyses extend to larger-scale circuits (DMN, frontal–temporal–sensory–motor, sensory–motor–insular–thalamic, and insula–cerebellum–occipital circuits) and are interpreted as hypothesis-generating.

DTI provides complementary insight into the microstructural substrates of PSD. The severity of white-matter injury—reflected by FA and MD metrics—is closely related to the severity of dysphagia, and adaptive white-matter changes may accompany recovery (59). Stroke is associated with disturbances of both functional and structural networks and with state-dependent reductions in functional-structural coupling (60). Therefore, this study included 20 healthy controls as a baseline reference to identify network sites with PSD abnormalities. Combined rs-fMRI and DTI analyses of SC-FC coupling sensitively index clinical impairment and recovery after PSD (46, 60).

Rs-fMRI studies indicate that acupuncture can activate swallowing-related cortical regions in PSD and enhance activity within central swallowing hubs, thereby promoting functional recovery of the cortical swallowing centers. FNIRS evidence suggests that acupuncture facilitates frontotemporal-sensorimotor network integration (61). However, PSD involves not only widespread cortico-cortical injury but also disruption of cortico-subcortical networks, and the mechanisms of structure-function reorganization remain insufficiently understood (51).

Building on this analysis hierarchy, we will examine whether acupuncture-related changes in structure-function coupling and circuit-level functional connectivity track clinical improvement over the 6-week intervention period, using healthy controls as a baseline reference.

We hypothesize that the Tiao Shen Li Yan acupuncture may improve swallowing function in PSD by enhancing integration within swallowing-related functional networks and promoting microstructural repair of inter-network white-matter pathways, thereby strengthening structure-function coupling across swallowing networks and facilitating functional reorganization of brain networks. In addition to the predefined ROI-based analyses, exploratory whole-brain analyses will also be performed to identify potential PSD-related brain regions that may not be included in the current swallowing network framework. These regions could become targets for future investigations. Importantly, structural and functional connectivity do not necessarily change in parallel during post-stroke recovery. Improvements in functional connectivity in the absence of structural recovery may reflect compensatory reorganization rather than true restoration (62), whereas structural recovery without corresponding functional gains may indicate suboptimal recovery. Therefore, quantifying structure–function coupling may provide mechanistic insight beyond assessing functional or structural metrics alone, by characterizing whether and how functional network reorganization remains constrained by (or diverges from) the underlying structural scaffold.

Overall, a major strength of this study is that it combines rs-fMRI and DTI to establish an “imaging-to-clinic” evidence chain that closely links clinical efficacy with mechanistic evidence. This approach is intended to delineate the structure-function coupling mechanisms by which the Tiao Shen Li Yan acupuncture modulates swallowing networks in PSD, and reveal the mechanism of brain functional network reorganization in PSD patients through acupuncture, while the inclusion of healthy controls enhances clinical relevance and interpretability.

However, this study has several limitations. For instance, the sample size is small and there is no sustained long-term follow-up. Because of budget and time constraints, only 46 patients will be included in this randomized controlled trial with a 6-week observation period. Future research should conduct multicentre trials, expand sample sizes, and extend follow-up periods to 3 months or longer to assess the persistence of clinical efficacy and neuroimaging effects, thereby enabling more in-depth exploration. Secondly, due to the nature of acupuncture research, complete blinding of the intervention is not feasible, which may introduce a risk of bias. Nevertheless, implementing random allocation concealment and maintaining complete blinding of evaluators and statisticians will help mitigate potential bias, thereby ensuring the rigor and credibility of the trial. In addition, task-based fMRI during swallowing was not included in the present protocol. Although task fMRI may provide more direct information on swallowing-related motor control and enable effective connectivity analysis, performing swallowing tasks during MRI scanning may introduce substantial motion-related artifacts and technical challenges, particularly in patients with PSD. Future studies could consider incorporating optimized task paradigms or multimodal approaches to further investigate task-specific neural mechanisms.

